#### Implementation {16c}

The study team will enroll participating pediatric practices. The allocation of the pediatric practices is done by the evaluating site. Participating practices will recruit and enroll patients. Patients are automatically assigned to interventions depending on their respective pediatric practice being in the intervention or the control group.

### Assignment of interventions: blinding

#### Who will be blinded {17a}

Due to the nature of the study, testing the STARKIDS intervention versus a control intervention, participating practices cannot be blinded to allocation. During recruitment of families, practices are asked not to reveal their allocation to potential participating families until families have decided on their participation.

#### Procedure for unblinding if needed {17b}

Not applicable since there is no blinding.

### Data collection and management

#### Plans for assessment and collection of outcomes {18a}

Outcomes are assessed at the three measurement time points and collected web-based through the STARKIDS e-health online platform which prevents duplicate measurements. Table 2 shows the applied questionnaires according to intervention modules. Further measurements (e.g., height, weight, somatic comorbidities, and blood levels) are assessed in the pediatric practices at the three measurement time points. The primary outcome BMI-SDS_LMS_ is calculated using the children’s height, weight (both measured in the pediatric practices), age, and gender.

#### Plans to promote participant retention and complete follow-up {18b}

Participant retention and complete follow-up are promoted by the monitoring of the pediatric practices in which families are. This is supported by mechanisms of the e-health online platform remembering families of, e.g., the follow-up questionnaires.

#### Data management {19}

All data is assessed pseudonymized. Data will be recorded directly in the online portal for the study by either pediatricians and medical assistants (e.g., blood levels, examination results) or participating parents or adolescents (questionnaire data). Data entry forms can only be filled in once on the respective measurement point to avoid double data entries and cannot be changed once completed. Pseudonymized data is securely stored within the server infrastructure of the coordinating center. More information about data management procedures and security can be retrieved from the project’s data security and IT security policy. Data monitoring will be conducted according to the Center of Clinical Trials (ZKS Tuebingen) internal standard operating procedures (SOPs) and a dedicated monitoring manual for the study.

#### Confidentiality {27}

All personal information on enrolled families is only collected on paper versions and kept in locked units at the participating practice and later at the coordinating center to be archived. All information collected on the e-health online platform is under the families’ aliases and therefore does not contain any personalized information that enables the identification of the families. Data at the coordinating center is kept separate from the lists containing personal information of families and can only be retrieved by dedicated study team members or be inspected by study monitors for quality checking and verification.

#### Plans for collection, laboratory evaluation, and storage of biological specimens for genetic or molecular analysis in this trial/future use {33}

As common in medical practices, blood samples are taken from participating children and adolescents. Blood levels of interest for the study team are transferred into the online platform by medical assistants. Therefore, there is no need for the storage of biological specimens by the study team.

## Statistical methods

### Statistical methods for primary and secondary outcomes {20a}

For the analysis of both primary and secondary outcomes a frequency comparison *χ*^2^c tests accounting for dependencies among observations within clusters [67] as well as generalized estimation equations (GEE) approaches will be used. The latter regression models will incorporate adjustment for relevant baseline covariates as well as concurrent covariates. A dichotomous variable capturing membership in the control vs. intervention group will be included in these models to assess the treatment effect as well as—with interaction terms—differential effectiveness in subgroups.

Analyses are conducted using all observations with available data (intention-to-treat) as well as the per-protocol subset of observations with adequate consideration of potential differences in results between these two strategies. Maximal utilization of data from families that eventually drop out of the intervention program will be secured and adequate steps will be undertaken to obtain at least measurements of the primary outcomes from these families after participation discontinuation.

In addition, cost-effectiveness and cost-utility analyses are performed. Adjusted total costs per capita, QALYs, and differences in total costs and QALYs between the control and intervention group are calculated using mixed-effects linear regression models with robust standard errors adjusted for relevant covariates at baseline. To account for uncertainty with regard to costs and effects, nonparametric bootstrappings are performed. The cost-effectiveness acceptability curves of the intervention group are calculated based on the net benefit approach. Therefore, multilevel mixed-effects linear regressions are used based on the net monetary benefit for different willingness-to-pay (WTP) thresholds. A long-term perspective on the macrosocial added value of STARKIDS will be performed with the help of decision-analytic modeling or state-transition modeling.

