**Methods:**

The STARKIDS intervention is evaluated in a cluster-randomized study design by comparing it with a control group receiving a one-time structured counselling in the pediatric practice. The study aims to include 1000 families with children/adolescents with overweight/obesity from 100 pediatric practices. The main outcomes are reduction in body mass index percentiles and improvements in children’s/adolescent’s quality of life, secondary outcomes refer to the contents of the intervention such as diet, physical activity, stress, and media habits. All outcomes are measured on three measurement time points: (T0) at baseline/inclusion in the study, (T1) baseline + 12 months which is the end of step 1 of the STARKIDS intervention, and (T2) baseline + 18 months which is the end of step 2 of the STARKIDS intervention.

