### Outcomes {12}

All outcomes are measured on three measurement time points: (T0) at baseline/inclusion in the study, (T1) baseline + 12 months, and (T2) baseline + 18 months. T1 marks the primary outcome measurement time point and T2 marks the secondary outcome measurement time point.

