#### Primary outcomes

There are two hierarchically structured primary outcomes: an objective parameter measuring weight development as the main primary outcome and a subjective parameter measuring self- and parent-reported quality of life of the children and adolescents. Weight development is measured from baseline to follow-up in BMI standard deviation scores (BMI-SDS or BMI *z*-scores) that are derived using the LMS method [20] (BMI-SDS_LMS_) with a representative German reference population [21, 22]. The (hierarchically structured) second primary outcome is a positive change of mean in children’s and adolescents’ quality of life from baseline to follow-up [23]. Primary outcomes are assessed at each of the three measurement points in the pediatric practice (BMI-SDS_LMS_) or online via a questionnaire (quality of life).

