### Sample size {14}

A total sample size of 1000 children and adolescents from 100 pediatric practices (on average 10 in each pediatric practice, with high variability of cluster sizes) was determined. This is based on a power calculation that takes dropout (adherence rate of 75%) and a cluster effect of 2 into account. With the projected final sample (750 individuals in 100 clusters), differences in proportions of participants that reach the target criterion (i.e., − 0.2 BMI-SDS_LMS_ reduction) between 14% (27% vs. 13%) and 17% (58.5 vs. 41.5%) are detectable with a maximum type I error rate of 5% and minimal power of 80% in a *χ*^2^ test.

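### The main primary outcome is continuous BMI-SDS change, but the only power statement concerns a responder proportion, and two unranked analyses are listed for it

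*Protocol article*

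**What the plan says.** Four parts of the protocol article bear on this point.

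- **Outcomes {12} and Primary outcomes.** "T1 marks the primary outcome measurement time point", that is, 12 months. "There are two hierarchically structured primary outcomes", with weight development first. "Weight development is measured from baseline to follow-up in BMI standard deviation scores". The second outcome is a positive change in mean quality of life. Neither definition contains a responder criterion.
- **Sample size {14}.** The power statement is about "differences in proportions of participants that reach the target criterion", the criterion being a "0.2 BMI-SDS_LMS_ reduction". With 750 analysed children in 100 practices and a cluster effect of 2, differences of "14% (27% vs. 13%) and 17% (58.5 vs. 41.5%) are detectable" at a maximum 5% type I error and at least 80% power, in a chi-square test. There is no other power statement.
- **Statistical methods {20a}.** "For the analysis of both primary and secondary outcomes a frequency comparison" by a cluster-adjusted chi-square test is listed alongside GEE regression with covariates. The two are not ranked, and the outcome scale for the GEE is not given.
- **Abstract, Methods.** "The main outcomes are reduction in body mass index percentiles", together with quality of life.

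**The concern.** The outcome definition, the quantity that was powered and the listed tests should all refer to the same variable. Here the definition is a mean change on a continuous scale, the powered quantity is a proportion, and the first listed test compares frequencies. A frequency test cannot test a change in mean without a cut-point, and the outcomes section supplies none.

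Three things are at stake. First, cutting a continuous measure at a threshold loses information. Second, with two unranked analyses of one primary outcome, the deciding test could be chosen after the results are seen. Third, the hierarchy orders BMI-SDS before quality of life but does not say which BMI-SDS result opens the way to the second outcome when the two analyses disagree.

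**Working it through.** **Inputs from Sample size {14}:** 750 analysed, cluster effect 2, 75% adherence, 5% type I error, 80% power, contrasts 27% vs 13% and 58.5% vs 41.5%.

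**Assumptions, because the article does not state them:** two-sided test; 1:1 allocation; the same cluster effect on both scales; BMI-SDS change normal with equal SD in both arms, so that a difference in responder rates reflects a shift of the mean.

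**Effective sample:** 750 / 2 = 375, or 187.5 per arm.

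**1. The plan's own figures.** Responder power = Φ{[Δ − 1.960·√(2p̄(1−p̄)/n)] / √[(p1(1−p1) + p2(1−p2))/n]}, with n = 187.5.

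- 27% vs 13%: (0.14 − 1.960 × 0.0413) / 0.0407 = 1.45, power 92.7%.
- 58.5% vs 41.5%: (0.17 − 1.960 × 0.0516) / 0.0509 = 1.35, power 91.2%.

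With a continuity correction these are 90.7% and 89.4%. The differences detectable at exactly 80% power are about 11.2 and 14.4 points (11.8 and 15.0 with the correction), not 14 and 17. The published pair is approximately matched if the 25% loss is taken off the 750 a second time (140.6 effective per arm) with the correction: 14.0 and 17.3 points. Because 80% is given as a minimum, the statement is conservative and not false.

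**2. The same contrasts on the continuous scale.** Implied shift d = z(p1) − z(p2); power = Φ(d/√(2/187.5) − 1.960), where √(2/187.5) = 0.1033.

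- 27% vs 13%: d = −0.613 + 1.126 = 0.51 SD, power 99.9%.
- 58.5% vs 41.5%: d = 2 × 0.215 = 0.43 SD, power 98.6%.

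**3. Cost of the cut-point.** Effective children per arm for 80% power:

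| Contrast | Continuous | Responder | Loss |
|---|---|---|---|
| 27% vs 13% | 60 | 127 | 1 − 60/127 = 53% |
| 58.5% vs 41.5% | 86 | 135 | 1 − 86/135 = 36% |

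As enrolment (× 2 arms × 2 / 0.75), this is about 320 against 677, and 459 against 720.

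**4. Detectable difference on the continuous scale.** (1.960 + 0.842) × 0.1033 = 0.29 SD at 80% power. The article gives no SD of BMI-SDS change. For an assumed SD of 0.2 to 0.5, this is 0.06 to 0.14 BMI-SDS.

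**5. Type I error if either test could succeed.** In 40,000 simulated null trials with 188 independent observations per arm, each test alone rejected in about 5%. At least one rejected in about 8.2% at a 20% response rate and 8.1% at 50%. For comparison, two independent tests would give 1 − 0.95² = 9.75%.

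**The case against.** The strongest reply is that this is a condensed article whose full protocol and analysis plan are not shown. Ranking the tests, choosing the GEE scale and stating the gatekeeping rule are commonly left to those documents. GEE can be fitted to continuous BMI-SDS, so much of the remedy may already be intended, and {20a} can be read as chi-square for categorical versions of outcomes and GEE for the rest. That section does not repeat the 0.2 threshold; the link comes from {14}. All of this stands, and it limits the claim. It does not remove the mismatch between Primary outcomes and Sample size {14}, which an analysis plan could not satisfy both ways as they are worded.

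A reader might go further and infer the following, which the article does not support:

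- **That the trial is underpowered.** The responder test has over 90% power for the stated contrasts. At a shift of 0.29 SD its power would be only 46% to 61% (13% and 44.3% control response), but 0.29 SD is the continuous test's own 80% point and not a planning effect in the article.
- **That the change would secure the trial against a small effect.** Background {6a} cites a standardised difference of −0.12. Power there would be about 21% on the continuous scale and about 15% for responders at rates near 50%, so it is low either way.
- **That the plan tests twice at 5%.** Neither analysis is labelled confirmatory, and nowhere does the article say that success on either counts.
- **That BMI percentiles are a rival third endpoint.** This is loose abstract wording for the same age- and sex-referenced BMI, which Primary outcomes makes specific.

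It is also fair to say that making the 0.2 responder rate the primary outcome would resolve the mismatch. That route keeps the efficiency loss and requires the outcome definition to be rewritten.

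**Conclusion.** The concern holds as an inconsistency between the defined primary outcomes, the powered quantity and the listed tests. The chi-square does not test the outcomes as defined. The cost is one of efficiency, about 36% to 53% of the effective sample for the contrasts in {14}, and not a shortfall against those contrasts. That size rests on the normal-shift, 1:1 and two-sided assumptions, since no SD is given.

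The error-rate point is conditional: about 8% against the stated 5% maximum, only if success on either test were accepted. The hierarchy is incomplete and not unworkable, because naming the test that opens the gate completes it.

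**What to change.** Before T1 data are analysed, which Interim analyses {21b} places after the second measurement point:

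1. Name one decisive analysis for the main primary outcome: the arm difference in BMI-SDS at T1 from a GEE or mixed model clustered on practice and adjusted for baseline BMI-SDS.
2. Test quality of life at T1 with the same type of model, only if the first result is significant.
3. Keep the 0.2 BMI-SDS responder comparison as a supportive analysis.
4. Add to Sample size {14} the detectable difference on the continuous scale, about 0.29 SD at 80% power with the stated numbers and cluster effect, and state the assumed SD. The responder figures can remain as supportive.

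No extra patients are needed. The costs are that the contrast used for planning becomes supportive, that an SD has to be assumed and justified, and that a protocol amendment is required after recruitment began on 1 April 2022.

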### Methods in analysis to handle protocol non-adherence and any statistical methods to handle missing data {20c}

Protocol non-adherence will be accounted for through the use of covariates capturing pertinent aspects of such non-adherence in the regression models mentioned under the “Statistical methods for primary and secondary outcomes {20a}” section as well as separate analyses for observation groups with difference adherence levels. Potentially different results between these groups as well as a potential role of adherence as a predictor of treatment effectiveness will be transparently considered and accounted for.

Provided that missingness of data can be plausibly considered as missing at random, multiple imputation techniques will be used in order to avoid untoward loss of non-missing information that could occur through the use of other strategies (e.g., inadequate listwise deletion).

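### The GEE models that estimate the treatment effect are to adjust for undefined concurrent covariates and for non-adherence, with no baseline-only model named as the main estimate

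*Protocol article*

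**What the plan says.** Section {20a} of the protocol article lists two approaches for both primary and secondary outcomes: a chi-square frequency comparison "accounting for dependencies among observations within clusters", and GEE regression models. Of the GEE models it says: "The latter regression models will incorporate adjustment for relevant baseline covariates as well as concurrent covariates". It then places the randomised comparison inside them: "A dichotomous variable capturing membership in the control vs. intervention group will be included in these models to assess the treatment effect". On analysis sets, the same section says: "Analyses are conducted using all observations with available data (intention-to-treat) as well as the per-protocol subset of observations".

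Section {20c} refers back to the {20a} models: "Protocol non-adherence will be accounted for through the use of covariates capturing pertinent aspects of such non-adherence in the regression models mentioned" there. It adds, as further work, "separate analyses for observation groups with difference adherence levels", and says that differing results between these groups will be considered openly.

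Two other parts of the article bear on this. The abstract says that "secondary outcomes refer to the contents of the intervention such as diet, physical activity, stress, and media habits". And the health-economic regressions, also in {20a}, are adjusted for covariates at baseline only.

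**The concern.** A randomised comparison estimates the effect of allocation as long as the model conditions only on variables that allocation cannot have changed. Two groups of covariates planned here may fail that condition.

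- **Concurrent covariates.** Set against baseline covariates, the term points to variables measured during follow-up. If one of them is something the programme is designed to change, adjusting for it removes the part of the effect that runs through it.
- **Non-adherence covariates.** Adherence arises after randomisation and means different things in the two arms. Under Intervention description {11a}, intervention families have 90-minute trainings every 3 months for a year plus an online platform, while control families have one counselling session of about 30 minutes. Adherence is also likely to reflect family motivation, which may itself predict weight change.

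At stake is the meaning of the arm coefficient for both primary outcomes, BMI-SDS and quality of life. Analysing every child with data does not give an intention-to-treat effect if the model conditions on adherence.

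**Working it through.** **Step 1. Reading the sections together.** {20a} puts baseline covariates, concurrent covariates and the arm term in one set of models. {20c} adds non-adherence covariates to that same set. Neither section confines these covariates to sensitivity, mediation or exploratory models, and neither requires them to be unaffected by allocation. No GEE restricted to baseline covariates is named as the main estimate. The document gives no figure on this point, so there is nothing to reproduce. Steps 2 to 4 use assumed values and show only what can happen.

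**Step 2. A covariate on the causal path.** Let the total effect be -0.20 BMI-SDS (assumed; the sample-size section uses the same value as an individual target for reduction) and let a share *s* of it run through the covariate. In a linear model the adjusted arm coefficient is -0.20 × (1 - *s*).

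| Share mediated | Adjusted coefficient | Simulated (n = 200,000) |
|---|---|---|
| 25% | -0.15 | -0.148 |
| 50% | -0.10 | -0.100 |
| 75% | -0.05 | -0.050 |
| 100% | 0.00 | -0.001 |

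Unadjusted estimates in the same simulations lay between -0.198 and -0.201.

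**Step 3. A covariate affected by arm and by an unmeasured prognostic factor, true effect zero.** Assume covariate M = 0.5·arm + c·U + noise with variance 1, and outcome Y = -0.2·U + noise, with U of variance 1. The adjusted arm coefficient is 0.2 × 0.5 × c/(c² + 1):

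- c = 0.3: 0.1 × 0.3/1.09 = +0.028
- c = 0.6: 0.1 × 0.6/1.36 = +0.044
- c = 1.0: 0.1 × 1.0/2.00 = +0.050

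The simulations gave +0.027, +0.041 and +0.047, against about 0.00 unadjusted.

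**Step 4. Adherence as covariate, true effect zero.** Let attendance in the intervention arm have mean *p* and slope *b* on the outcome (*b* is negative if motivated families both attend and lose weight). Let every control child be coded d₀. The slope is then estimated from the intervention arm alone, and the arm coefficient is *b* × (d₀ - *p*). Assume *p* = 0.75.

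| Assumed *b* (SDS, none to full attendance) | Controls coded 1: *b* × 0.25 | Controls coded 0: *b* × (-0.75) |
|---|---|---|
| -0.08 | -0.02 | +0.06 |
| -0.40 | -0.10 | +0.30 |
| -0.72 | -0.18 | +0.54 |

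The same children yield a spurious benefit under one coding and a spurious harm under the other. If adherence is instead measured on a common scale with the same distribution in both arms, such as questionnaire completion, the mean difference is zero and so is the bias.

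A simulation with 100 practices of 8 children, intraclass correlation 0.11, SD of change 0.4 and no true effect agrees. With controls coded 1, the bias ran from about -0.02 to -0.18, and rejection at the 5% level from about 8% to 99%, as the motivation–outcome correlation rose from 0.1 to 0.4 and the attendance–motivation correlation from 0.5 to 0.9. On a common scale the bias was 0.00 and rejection about 5%.

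**The case against.** The strongest reply has four parts.

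1. **No concurrent covariate is named.** A reader might infer that diet, activity, media use and stress will be adjusted for. The article does not say so: that list describes secondary outcomes. A time-varying covariate that allocation cannot affect, such as calendar or pandemic period, would do no harm. This stands, and it limits the first half of the point to what the wording permits. It does not help the second half, because non-adherence is named explicitly.
2. **A covariate-free analysis is also planned.** The cluster-adjusted chi-square test comes first in {20a} and is the type of test on which the sample size rests. It is untouched by this problem. This also stands, so it would be wrong to say that every planned analysis of the treatment effect is compromised. But the text does not make it the main analysis, and it assigns assessment of the treatment effect to the GEE models.
3. **The adherence-level analyses are additional.** A reader might infer that they should be withdrawn. They do not replace the main comparison, and labelling them exploratory is enough.
4. **The covariate list may be left to a fuller document.** The list can be. The rule that concurrent and non-adherence covariates enter the effect model is stated here, and a fuller plan that followed it would carry the problem forward.

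**Conclusion.** The point holds for the GEE models. As written, the arm coefficient may be conditioned on concurrent variables that allocation affects and is to be conditioned on non-adherence, and no baseline-only GEE stands as the main estimate. For any covariate affected by allocation, that coefficient is not the intention-to-treat effect. The authors' own health-economic models adjust for baseline covariates only.

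The size is unknown. The attenuation in step 2 rests on an assumed mediated share. The distortion in steps 3 and 4 rests on assumed links between motivation, attendance and outcome, and on how control-arm adherence is coded, which the article does not fix. It ranges from none, when adherence is comparable across arms, to substantial otherwise. No single row is this trial's expected bias.

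A reader might also be tempted to turn attenuation into a loss from the stated 80% power. The article does not support this: the 80% is a minimum, and it belongs to the chi-square comparison of proportions, not to the GEE.

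**What to change.** - **In {20a}:** state that the treatment effect is estimated in a GEE adjusted only for variables fixed at or before T0, such as the baseline value of the outcome and the two stratification factors (urban or rural area; potential high recruiter or not). Delete the concurrent-covariate clause from that model.
- **In {20c}:** remove non-adherence covariates from that model. Label analyses with concurrent covariates, analyses with adherence covariates and analyses by adherence level as supplementary or exploratory.
- **Optional:** a mediation analysis or a complier-average analysis may be added as supportive work. Neither is needed to resolve the point. A complier-average analysis would have to justify its assumption that allocation acts only through the adherence measured, which is open to question because families also use the online platform between trainings.

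The cost is a wording change in two sections. No new data, visits or participants are needed.
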